#### Randomisation

In each country, a total of 36 sites will be selected and matched into 12 trios based on the specified criteria. Within each trio, the study sites will be randomly assigned to one of three study arms at a 1:1:1 ratio. This randomisation process will be repeated 12 times, once for each trio. The randomisation process will not have any restrictions, and blinding (masking) of participants and providers cannot be implemented except for data analysts who will handle the study data independently. The study clusters will include all consecutive and eligible participants until the total sample size of 7920 participants is reached.

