#### Statistical analysis

We will prepare a comprehensive statistical analysis plan. Participants will form the unit of analysis and the clustered nature of the data will be accounted for. All analyses will be by intention to treat. For continuous variables, we will compute means, SD, minimum and maximum values, and for categorical variables, we will compute frequencies and percentages. We will look at the distribution of variables and see if there are any outliers as part of data quality control and descriptive analysis. Descriptive statistics will be tabulated for individual clusters and aggregated across clusters. Within each of the three groups/arms of the study (two experimental and one control), outcome differences between final (12 months after enrolment) and intermediate (6 months after enrolment) outcome measurements will be obtained, and these changes will be compared between the control group and each of the two experimental groups. For categorical outcomes, χ^2^ tests for two independent proportions will be used, and for continuous variables, Student’s t-tests for two independent means will be used. We will use IBM SPSS Statistics 25, R V.3.6.2, STATA V.16.1 or SAS V.9.4 statistical packages for the analysis. The findings will be presented using the CONSORT Statement checklist from 2010 and its extension for cluster studies.^45^

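### The between-arm tests named in the protocol assume independent women and so do not match its own promise to account for clustering by health centre

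*Protocol article*

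**What the plan says.** All references are to the protocol article; no separate analysis plan is shown.

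- **Unit of randomisation (Randomisation).** "In each country, a total of 36 sites will be selected and matched into 12 trios based on the specified criteria". Then: "Within each trio, the study sites will be randomly assigned to one of three study arms at a 1:1:1 ratio". Recruitment runs "until the total sample size of 7920 participants is reached".
- **General rule (Statistical analysis).** "Participants will form the unit of analysis and the clustered nature of the data will be accounted for". No method for doing so is given.
- **Comparison (Statistical analysis).** Differences between the 6-month and 12-month measurements are obtained within each arm, and "these changes will be compared between the control group and each of the two experimental groups".
- **Named tests (Statistical analysis).** For categorical outcomes, chi-squared "tests for two independent proportions will be used, and for continuous variables", Student's "t-tests for two independent means will be used".
- **Further detail (Statistical analysis).** "We will prepare a comprehensive statistical analysis plan".

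The section mentions no mixed model, GEE, design-effect correction or centre-level analysis. The article states no ICC, design effect or significance level.

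**The concern.** A two-sample test on individual women takes its standard error from the spread between women and treats each woman as a separate piece of evidence on the arm difference. Here the arm was assigned to the centre. Women at one centre share staff, supplies and catchment, and part of the autonomy outcome is a rating of how that centre's staff behaved. The article itself gives reasons to expect centres to differ. The Cluster RCT section matches them on workload, method range, staffing, setting and district factors thought able to affect the outcomes. The site criteria admit both high- and low-performing facilities.

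With positive correlation inside centres, the standard error from either named test is too small and the interval too narrow. An ineffective counselling package could then be declared effective against control too often, in either of the two planned contrasts. The general rule points one way and the named tests the other, so an analyst who works from this section cannot tell which governs.

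**Working it through.** **The plan's own figure.** The sample size cannot be re-derived, because no effect size, power, significance level, ICC or dropout is given. The arithmetic does fit two countries of 36 centres: 2 × 36 = 72 centres, and 7920/72 = 110 women per centre. That gives 12 centres per arm in each country, 24 per arm overall, and 24 × 110 = 2640 women per arm.

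**Inputs**
- m = 110 women per centre, from the Randomisation section, before any loss to follow-up.
- Two-sided 5% level: assumed.
- ICC: assumed, 0.01 to 0.10, with 0.001 and 0.005 as low values.

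**Formulas**, for a single measurement, unadjusted test and no allowance for matching:
- Design effect DE = 1 + (m − 1) × ICC = 1 + 109 × ICC.
- True two-sided error = 2 × [1 − Φ(1.96/√DE)].
- Factor by which the interval should be wider = √DE.

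| ICC (assumed) | DE | √DE | True error of a nominal 5% test |
|---|---|---|---|
| 0.001 | 1.109 | 1.05 | 6.3% |
| 0.005 | 1.545 | 1.24 | 11.5% |
| 0.01 | 2.09 | 1.45 | 17.5% |
| 0.02 | 3.18 | 1.78 | 27.2% |
| 0.05 | 6.45 | 2.54 | 44.0% |
| 0.10 | 11.9 | 3.45 | 57.0% |

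**Check by simulation.** Data were simulated with no true effect and 110 women per centre: binary outcomes with 24 or 12 centres per arm, continuous outcomes with 24. At ICC 0.01, 0.05 and 0.10 the individual-level tests rejected in about 16% to 19%, 42% to 44% and 56% to 57% of runs. A t-test on centre means rejected in about 4.5% to 6.4%. The 6.4% comes from the smallest set (1500 runs, standard error √(0.05 × 0.95/1500) = 0.6 percentage points). These simulations were unmatched and used a single measurement.

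**Sensitivity to cluster size**
- With 20% loss assumed, 0.8 × 110 = 88 women per centre. DE is 1.87 at ICC 0.01 and 9.70 at 0.10, and the error is 15.2% to 52.9%.
- If 7920 were meant per country, 7920/36 = 220 per centre and the error would be 27.3% to 68.2%. The Abstract gives 7920 as the study total, so 110 is the natural reading.

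**Sensitivity to matching.** If centre effects within a trio have correlation ρ, the variance inflation that the naive test misses becomes DE − m × ICC × ρ. With ICC 0.05 and an assumed ρ of 0.5, this is 6.45 − 110 × 0.05 × 0.5 = 3.70, and the error is 2 × [1 − Φ(1.96/√3.70)] ≈ 31% instead of 44%. Inflation disappears only when m × ρ reaches m − 1, that is ρ ≥ 109/110 ≈ 0.99.

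**The case against.** The strongest defence is that the section states the general rule first, announces a full analysis plan and cites the CONSORT extension for cluster trials. Cluster-adjusted forms of both tests exist, such as a chi-squared statistic corrected for the design effect or a t-test with inflated variance. The article never says that the tests are unadjusted. A reader might infer that the trial will ignore clustering and will therefore carry a false-positive rate of 17% to 57%. The document does not support that: it promises the opposite and states neither an ICC nor a significance level. The 17% is not a floor either, since a low ICC gives 6% to 12%. It is also too strong to say that the promise and the tests could never be reconciled.

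Two further points stand. The planned comparison is a change from 6 to 12 months. Stable differences between centres largely cancel in a within-woman change, at least for a continuous score, so the relevant ICC may be lower than for a single measurement. Matching also lowers the residual between-centre variance, so the tabulated rates are upper values for their ICCs.

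What does not stand is that this is a detail left to the analysis plan. The article could have stayed silent. Instead it fixes women as the unit and names tests whose description specifies independence, without calling them adjusted. Reading the t-test as a centre-level test does not help, because participants are the stated unit and the companion chi-squared test compares proportions of women.

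**Conclusion.** The mismatch is real and lies in the current text of one section: a promise to account for clustering, followed by two individual-level tests that do not do so as named. The direction of the error is clear, towards too many false positives. Its size is conditional. Unadjusted, at an assumed two-sided 5% level and about 110 women per centre, the rate would be about 17.5% to 57% for an assumed ICC of 0.01 to 0.10, and about 6% to 12% for 0.001 to 0.005. Loss to follow-up, the use of change scores and good matching would each be likely to lower these figures. None would be expected to remove the inflation unless the remaining between-centre variation were close to nil. The figures show what is at stake if the tests are followed literally; they are not a forecast of the trial's error rate.

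**What to change.** Replace the two individual-level tests in the Statistical analysis section, and carry the same wording into the analysis plan. Name one of these for each contrast with control:

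- **Model-based.** A mixed model, or GEE with a small-sample correction, with centre as the cluster and terms for country and matched trio (trios lie within country, so trio indicators already contain country). Specify small-sample inference for binary as well as continuous outcomes, because demand satisfied and modern contraceptive use are binary.
- **Centre-level.** Summarise each centre and analyse the summaries paired within trio. Each contrast then rests on 24 within-trio differences, 12 per country. An unpaired comparison of 24 with 24 centres would control the error rate but ignore the trios and country, and its intervals would be wider than necessary if the matching works.

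Report each effect estimate with its 95% interval, and the observed ICC.

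The cost is wording only. Data collection, sample size and conduct do not change. Intervals will usually be wider than those from the unadjusted tests.

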### Patient and public involvement

Patients or the public were not involved in the design, or conduct, or reporting, or dissemination plans of this research.

### Ethics and regulatory aspects

We adhered to The Ottawa Statement on the Ethical Design and Conduct of Cluster Randomised Trials when designing this experiment.^46^ The Research Project Review Panel (RP2) of the HRP peer-reviewed the protocol, and RP2 and the WHO Research Ethics Review Committee, Geneva, Switzerland (Pakistan: ERC 006232 and Nigeria ERC: 006523), approved it and so did the IRB of Research and Development Solutions (IRB No:00010843) in Pakistan. While the Ministry of Health, Kano State of Nigeria (NHREC 17/03/2018) and Lagos Research Ethics Committee in Nigeria (LREC/06/10/2180) provided ethical approvals for the Nigeria study.

This research is grounded in human rights principles, specifically participation in the form of participatory action research. The existing literature suggests promise for the success of our proposed approach. For instance, a synthesis of evidence on community-based participatory research across various settings has shown that collaboration among community partners, researchers and organisations has led to community-level actions that improve health and well-being while reducing health disparities.^47^ This collaborative process has also contributed to strengthening community capacity in research and leadership skills. Another review highlighted that participatory action research can ensure that research is culturally and logistically appropriate, enhance recruitment capacity, foster professional capacity and competence among stakeholder groups, facilitate productive conflicts followed by constructive negotiation, improve the quality of outputs and outcomes over time, enhance sustainability of project goals beyond funding periods and during gaps in external funding, and drive system changes and new unforeseen projects and activities.^48^
